Most cervical cancers occur in women who have not undergone screening or are screened less frequently [10]. The National Cervical Screening Program (NCSP) shows that the target level of 80% of *wāhine* Māori screened within the previous 3 years is not achieved in any region; once screened, there is a failure to achieve a timely diagnosis and treatment of abnormalities for *wāhine* Māori [9]. Fewer *wāhine* Māori have a colposcopy within an appropriate time frame following a high-grade abnormality when compared with non-Māori women. Furthermore, the proportion of women who had no record of any subsequent follow-up at 90 days is 4.4% for European women but 8.6% for *wāhine* Māori [11].

The current national screening approach for cervical cytology involves an invasive procedure using a speculum, which requires attending a clinic with associated transport and other costs. Cervical screening in rural Aotearoa is performed by the primary care nurse or physician, and the tests are sent to a centralized laboratory for analysis. The results are returned to the primary care clinician, who then notifies the patient. If the result is abnormal, the clinician writes a referral letter to a gynecologist requesting an appointment for a colposcopy. Hospital departments then control all further investigations and treatments. Delays can occur at each point, which in turn create barriers to access, timely diagnosis, and treatment [12].

Human papillomavirus (HPV) is the causative agent of cervical cancer. Infection with certain oncogenic (cancer forming) high-risk types of HPV cause changes in the cells of the cervix that can lead to cancer. Compared with cytology, HPV-based screening is a better test; it provides 60% to 70% greater protection against developing invasive cervical cancers [13,14]. The World Health Organization recommends that all countries transition to HPV testing as the primary method for cervical screening [15-17]. It is also internationally recognized that a self-taken swab that uses molecular amplification testing platforms such as polymerase chain reaction is as effective in detecting high-risk HPV (hrHPV) as a clinician-taken sample [18,19].

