### Outcomes

The primary outcome is the proportion of women having a colposcopy within 20 working days from the test, for those women with a positive test result for hrHPV.

Secondary outcomes are of those with a positive hrHPV test result:

Proportion of women having a colposcopy within 40 working days of the testProportion of women having a colposcopy within 20 working days of referralProportion of women having a colposcopy within 40 working days of referralTime from test to colposcopyTime from referral to colposcopyNumber of high-grade lesions (cervical intraepithelial neoplasia and carcinoma)Planned treatment for women with high-grade histology at colposcopy.

Secondary outcomes include of all women taking the HPV test:

The proportion of women who test positive for hrHPVThe proportion of women who test negative for hrHPVThe proportion of women who have invalid resultsThe proportions due for screening, underscreened, or never screened.

Qualitative outcomes are as follows:

To explore and understand the successes and challenges of both pathways from the perspectives of the governance groups, clinical staff (nurses, doctors, *kaiāwhina* [nonclinical community health workers], and specialists), and women (including *whanau* or family supporters) at both sitesTo understand this new screening pathway to advise and inform a more culturally responsive NCSP.

On the basis of the percentage reported for *wāhine* Māori throughout Aotearoa, we estimated that 56.4% of women in the control arm will have a colposcopy within 20 working days following referral for a positive HPV test [30]. We aim to detect a 50% increase (relative risk 1.5) from 56.4% to 84% in the primary outcome for the intervention arm. A sample size of 80 women (n=40, 50% in each arm) in a 2-period, 2-cluster randomized crossover trial will provide 80% power at 2-sided α of .05 to detect a 50% increase in the intervention arm. With only 2 practices serving as the clusters, the sample size does not account for the cluster effect, which will be considered as a fixed effect in the final analysis.

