The order of treatment for each practice has been randomly allocated by the study statistician using computer-generated random numbers. Using the eligible population list for each practice, the research team randomly allocated half of the under- or never-screened women to priority recruitment in the first study period and half to the second study period. This was done to reduce the potential bias from unequal recruitment of under- or never-screened women between the 2 study periods. The lists for priority recruitment were provided to the practices.

As this is a 2-period, 2-cluster randomized crossover trial, each practice acts as a comparator for the other practice during the trial period.

Blinding of participants and clinicians is not possible. The 2 trial statisticians will be unblinded and compile the data set and conduct the statistical analysis.

The inclusion criteria were women aged 24.5-69.9 years eligible for cervical screening in these 2 rural areas. In line with the current NCSP protocol, women can present for the first screen up to 6 months before their 25th birthday and be included. Women can present for screening up to 6 months before their due date and be included [31]. Women who are due for screening or who are underscreened (underscreened is defined as never screened or ≥4 years since last screening) are eligible.

Women with heavy bleeding at the time or those using a vaginal cream that might interfere with the test are asked to return at a later date. Women who opt for cervical cytology or whose general practitioner advises a speculum examination and cervical cytology can also participate in the study by taking an HPV self-taken (or clinician taken) swab first. Women who have symptoms such as abnormal bleeding can still be offered an HPV test, but they will also be seen and assessed by a general practitioner and may require assessment by secondary gynecology services despite a negative hrHPV test.

Primary care clinicians (physicians and nurses) and *kaiāwhina* at both sites received training from the research team on how to obtain informed consent from women. Training was conducted in person or via a video link. Trained clinicians or *kaiāwhina* obtain informed consent from women in both pathways for a copy of their HPV results (and if colposcopy is required, copies of histology results) to be sent to the researchers and the ordering health practitioner.

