### Data Collection and Analysis

Regular 3 monthly visits to the research sites are made by the members of the research team. These visits include updating the clinic staff on any amendments and audits of the PMS to ensure that the results are documented accurately and coded, given to women, and followed up appropriately. The research team’s molecular scientist visits regularly to audit the POC instruments and sample testing process compliance. The practices have ownership of their data and all the results. Researchers are readily available via phone and email to support practices.

The ordering clinician and practices have the primary responsibility for follow-up. For clinical safety, the unblinded study statistician checks for colposcopy referrals and attendance. This is checked no sooner than 3 months from the hrHPV test date, so the primary outcome is not influenced but ensures that practices can contact any woman who has not yet attended a colposcopy appointment.

Follow-up colposcopy and treatment performed within the public health service are free for Aotearoa citizens and permanent residents. The new NCSP will start in September 2023, and the women in this trial will be registered with the new program appropriately.

Data collection and management are conducted as follows: copies of consent forms, POC test results, and laboratory results are provided to the research team by the study sites and used to track recruitment and monitor safety. Every 6 months, the colposcopy services provide data to the study statisticians: colposcopy attendance and date, colposcopy assessment and outcome, cytology result (if any) at colposcopy, histology, treatment plan, and any treatment provided. No other research team members have access to colposcopy data.

Each person using a health or disability support service in Aotearoa has a unique National Health Index (NHI) number [37]. The research team provides the NHI numbers of the participating women to the National Screening Unit to obtain cervical screening and clinical history at the start of the study period from the NCSP. The NHI number is also used to obtain ethnicity, the deprivation index (socioeconomic status), and age from the NHI data set.

The NHI number is replaced with a unique study code in all research data sets for analysis. No individuals will be identifiable in the reporting of study findings.

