All statistical analyses will be performed using SAS (version 9.4; SAS Institute) and R (version 3.4.2; R Foundation for Statistical Computing). Analyses will be intention to treat and conducted at the individual participant level. All tests of significance are 2-tailed and at a 5% significance level throughout the analyses. Continuous variables will be compared with *t* tests or Mann-Whitney *U* tests, and categorical data will be compared using chi-square tests, as appropriate.

A generalized linear regression model with a binomial distribution will be used to analyze binary outcomes, a linear regression model will be used to analyze continuous outcomes, and the cluster design will be taken into account in the analyses. For the primary outcome, both unadjusted and adjusted analyses for potential covariates measured at baseline will be conducted (eg, deprivation index and age). Unadjusted and adjusted odds ratios will be reported with corresponding 95% CIs and associated *P* values. Relative risks will also be estimated using Poisson regression models with robust error estimates. For the primary outcome, participants with missing data will be assumed as not having a colposcopy within 20 working days. Sensitivity analyses will be conducted for the primary outcome to assess the robustness of the results, which will include per-protocol analyses (where participants with any protocol deviations will be excluded). Additional sensitivity analyses may be considered, such as the potential impact of COVID-19 restrictions or extreme weather events. Subgroup analyses will be conducted for ethnicity, screening history, HPV type, and symptoms (if the numbers are sufficient). Time to notification and time to colposcopy will be analyzed using Kaplan-Meier curves, log-rank tests, and Cox proportional hazard models.

Qualitative data will be analyzed thematically. This will involve reading and rereading the transcripts, coding sections of data inductively, and combining and rearranging the codes to create themes and subthemes [39]. NVivo12 (QSR International) qualitative data analysis software will be used to assist in the coding and theming of data. In reporting the themes, feedback from participants will be written about in a way that groups their talk about common issues and how these issues are interrelated.

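### A timely colposcopy at a service that does not report to the trial would be scored as a failure; the existing NHI link may offer a cheap check before the missing-as-failure rule is applied

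*Protocol article*

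**What the plan says.** All of this is in the Protocol article.

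- **Outcome** (Outcomes): "The primary outcome is the proportion of women having a colposcopy within 20 working days from the test", among women positive for hrHPV. The definition is not limited to particular providers.
- **Scoring rule** (Data Collection and Analysis): "For the primary outcome, participants with missing data will be assumed as not having a colposcopy within 20 working days". The sensitivity analyses named are per-protocol and, as possibilities, the effects of COVID-19 restrictions and extreme weather. None is aimed at this rule.
- **Source of dates** (same section): "Every 6 months, the colposcopy services provide data to the study statisticians: colposcopy attendance and date". The services are not listed. Both pathways refer women to the hospital (Intervention Description), and locality authorization came from the Tairāwhiti and Hawke's Bay boards (Ethical Considerations).
- **Register link** (Data Collection and Analysis): NHI numbers go to the National Screening Unit "to obtain cervical screening and clinical history at the start of the study period from the NCSP". No later extract is described.

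**The concern.** Missing-as-failure is sound when having no record means that the woman was not seen. Here it may also mean that she was seen by a service that does not send data to the trial. The outcome definition would count her as a success and the scoring rule would count her as a failure.

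Every such case lowers the observed attendance rate of its pathway. If cases occur in equal proportion in both pathways, the absolute difference and the odds ratio shrink and power falls. If they occur mainly in one pathway, the relative risk is biased as well. The article reports odds ratios with confidence intervals and P values for the primary outcome, so even equal loss affects a headline estimate. The article already describes a link that might resolve the doubt, but does not say that it will be used for outcomes.

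**Working it through.** **Inputs from the Outcomes section.** Control rate 56.4%, intervention rate 84% (relative risk 1.5), 40 women per arm, two-sided α of 0.05, 80% power. The 56.4% is timed from referral and the outcome from the test. That is a separate matter, and the figure is used here only as the plan's own design value.

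**Assumption.** Let m be the share of timely colposcopies that the service return does not capture. The documents give no value, so m is varied from 0 to 20%.

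**Step 1: reproduce the plan's sample size.** Pooled normal approximation, n per arm = [1.96·√(2·p̄·(1−p̄)) + 0.8416·√(p1(1−p1) + p2(1−p2))]² / (p2−p1)². With a relative risk of exactly 1.5, p2 = 1.5 × 0.564 = 0.846 and p̄ = 0.705. Then n = (1.264 + 0.516)² / 0.282² = 39.9, or 40 per arm and 80 in total, with power 80.1%. The plan's figure is reproduced. With the rounded 84%, power at 40 per arm is 78.1%. That is the baseline below.

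**Step 2: equal loss in both pathways.** Observed rate = true rate × (1 − m).

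At m = 5%: 0.95 × 56.4 = 53.6% and 0.95 × 84 = 79.8%.
- Difference: 79.8 − 53.6 = 26.2 points, against 84 − 56.4 = 27.6.
- Odds ratio: (0.798/0.202) / (0.5358/0.4642) = 3.42, against (0.84/0.16) / (0.564/0.436) = 4.06.
- Relative risk: the factor (1 − m) cancels, so it stays at 0.84/0.564 = 1.49.

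| m, both pathways | Difference (points) | Odds ratio | Relative risk | Power, 40 per arm |
|---|---|---|---|---|
| 0 | 27.6 | 4.06 | 1.49 | 78.1% |
| 2% | 27.0 | 3.77 | 1.49 | 75.2% |
| 5% | 26.2 | 3.42 | 1.49 | 70.9% |
| 10% | 24.8 | 3.01 | 1.49 | 63.9% |
| 20% | 22.1 | 2.49 | 1.49 | 51.2% |

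**Step 3: unequal loss, either way.** If 10% is missed only in pathway 2, the relative risk is 0.84 / (0.9 × 0.564) = 1.65. If 10% is missed only in pathway 1, it is (0.9 × 0.84) / 0.564 = 1.34. Nothing in the documents selects between these.

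**Step 4: scale in women.** The Results section gives 54 hrHPV-positive tests in period 1 over both pathways. If period 2 yields the same, there are about 108 in all, or 54 per pathway. A 5% loss is then 0.05 × 0.564 × 54 = 1.5 women in pathway 2 and 0.05 × 0.84 × 54 = 2.3 in pathway 1, about four in total. At 54 per pathway, power is about 89% with full capture and about 83% at 5% loss.

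**The case against.** The strongest reply is that the gap is not shown to exist. The reporting services are plural and unnamed, so they may cover every place where participants are seen. Both pathways send women to the hospital, public colposcopy is free for citizens and permanent residents, and transport and other support are offered in both pathways. No statement says that any participant is seen elsewhere. This stands: the frequency is unknown and may be close to zero.

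A reader might infer that the rule favours pathway 1, because women kept waiting in pathway 2 go elsewhere. The documents do not support that. To be misclassified, a woman must be seen elsewhere within 20 working days of the test. One who leaves after a long wait will mostly be past that limit and is correctly scored as a failure. Each site also runs both pathways, so a stable difference between sites in capture largely balances.

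A reader might also infer that the register certainly holds the missing dates. The article calls the 20-working-day measure a national performance indicator, takes the 56.4% from national figures for wāhine Māori, and reports national follow-up ("the proportion of women who had no record of any subsequent follow-up at 90 days is 4.4% for European women", with a higher figure for wāhine Māori). That makes the dates plausible. It does not establish that the Unit holds them for every provider or would release them for each woman.

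Other routes could catch some cases. Consent covers histology ("and if colposcopy is required, copies of histology results) to be sent to the researchers"), and the unblinded statistician checks attendance no sooner than 3 months after the test. But histology exists only where tissue is taken, and the later check is described as a safety measure, with no stated source and no stated role in scoring the outcome.

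Finally, an article condenses the full protocol, which may list the services and the reconciliation steps. That lowers the weight of the point. But the article itself fixes the rule, the source and the limited use of the link, and these three leave the gap when read together.

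**Conclusion.** The point holds as a cheap improvement, not as a demonstrated bias. As written, a timely colposcopy at a non-reporting service would be scored as a failure, against the outcome's own definition, and no stated step checks the register first. Under the assumed equal 5% loss, the effect is 1.4 points on the difference and a fall in the odds ratio from 4.06 to 3.42. The relative risk is unaffected. A change in the relative risk requires capture to differ between pathways, and the documents show neither that it does nor in which direction. All sizes rest on an assumed m. The missing-as-failure rule is itself a reasonable default once absence of a record has been verified.

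**What to change.** At the end of follow-up, use the existing NHI link to ask the National Screening Unit for any colposcopy date for every hrHPV-positive participant, if it can supply these. Count a colposcopy at any provider within 20 working days of the test as a success. Score failure only when neither the service return nor the register shows one. Name the reporting services, so that the reader can judge how much the register check adds; if the Unit cannot supply dates, say so.

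The cost is one extra data request for roughly 100 women and possibly a minor ethics or data-use amendment. It needs no added visits or participants.

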### Intervention Description

#### Overview

The site randomized to pathway 1 for the first period nominated ≥2 primary care clinicians and *kaiāwhina* to be trained by qualified members of the research team in the operation and daily quality audit of the Cepheid GeneXpert IV instrument. POC training was overseen by the research team’s molecular scientist in the week before recruitment began. This consisted of orientation and familiarization runs using contrived samples and official training directly from Cepheid via a video link. The technology is robust, but user training and support are vital. Only those holding a training certificate issued by Cepheid are authorized to run patient samples. Regular in-person, on-site POC updates run throughout the trial. User and instrument proficiency testing is built into the implementation process and conforms to the New Zealand Best Practice Guidelines for Point-of-Care Testing [32]. In addition, the research team and site clinicians involved in POC testing are participants in the Royal College of Pathologists of Australasia Quality Assurance Program [33]. The Cepheid GeneXpert IV instruments used in this study are loaned from the Australian Centre for the Prevention of Cervical Cancer.

A 2- to 4-week washout took place between the 2 study periods. The second site received the same training schedule on how to use the Cepheid GeneXpert IV instrument, and the instruments were transported, set up, and tested at the second study site.

#### Pathway 1

Following self-collection, the vaginal sample is processed onsite by the Cepheid GeneXpert IV instrument, taking approximately 1 hour, and the result is documented in the patient management system (PMS). The intention is for women to receive the HPV test result in person onsite, as soon as the test result is available.

Women with hrHPV-positive results receive immediate on-site information about the result, its significance, the next steps, and support. An appointment for colposcopy is made straight away by a phone call to the appointment clerk at the hospital. This phone call is followed up with a referral letter from the referring primary care clinician.

Women with hrHPV-negative results are informed of the result and its significance and advised that they will not need screening for 5 years.

If a woman is unable to stay for an hour to receive her test result, her contact details are taken, and she is contacted as soon as the result is available.

#### Pathway 2

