Following vaginal sample self-collection, the woman is asked how she would prefer to receive the result (by SMS text messaging, phone, or in person). The sample is then transported at room temperature to the diagnostic laboratory as part of the practice’s routine laboratory collection. hrHPV genotyping is performed using the Roche Cobas 4800 system. This system detects 14 hrHPV types (16, 18, 31, 33, 35, 39, 45, 51, 52, 56, 58, 59, 66, and 68) and provides a result which distinguishes types 16 and 18 from “other” high-risk types [34]. The use of dry vaginal swabs has been validated in international published studies, and the laboratory is undertaking this testing “off-label” [35,36]. The samples are disposed of in line with the standard pathology laboratory procedures. Test results are sent electronically (encrypted as other routine results) to the ordering primary care clinician and entered into the PMS, as cytology results would be.

Women with hrHPV-positive results are informed of the result and its significance by phone or in person. Information regarding the next steps and support are provided. The primary care clinician sends a referral letter to the colposcopy service at the hospital. The woman is triaged for a colposcopy appointment, and the appointment time is sent to the woman by mail, with or without phone follow-up.

Women with hrHPV-negative results are informed of the result and its significance and advised that they will not need screening for 5 years.

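### A Cox hazard ratio is a poor summary for time to notification, because a one-hour result is built into one pathway only

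*Protocol article*

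**What the plan says.** In the protocol article, the statistical paragraph of Data Collection and Analysis assigns methods to two time variables: "Time to notification and time to colposcopy will be analyzed using Kaplan-Meier curves, log-rank tests, and Cox proportional hazard models".

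The Intervention Description sets out how each pathway produces a result. In Pathway 1, "the vaginal sample is processed onsite by the Cepheid GeneXpert IV instrument, taking approximately 1 hour", and "The intention is for women to receive the HPV test result in person onsite, as soon as the test result is available". There is an exception: "If a woman is unable to stay for an hour to receive her test result, her contact details are taken", and she is contacted once the result is ready. In Pathway 2, "The sample is then transported at room temperature to the diagnostic laboratory", with the practice's routine collection. The result returns electronically to the clinician, who then has the woman told.

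The Outcomes section lists time from test to colposcopy and time from referral to colposcopy among hrHPV-positive women. It does not list time to notification.

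Two general rules stand in the same analysis section. One says that "a linear regression model will be used to analyze continuous outcomes". The other, beginning "Continuous variables will be compared with", names t tests or Mann-Whitney U tests, as appropriate. Neither names a time outcome.

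**The concern.** A Cox hazard ratio summarises two arms well when the ratio of their event rates is roughly constant over time. Here the intervention is, in part, the removal of the laboratory wait. One arm is meant to have a block of notifications within hours of the test, at a time when the other arm can have few or none. After that block, the few pathway 1 women still waiting are told after ordinary delays, much like women in pathway 2. One ratio averaged over those two phases describes neither.

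The trial could then report a large, unstable number that a reader cannot turn into hours or days, when the same data would give two direct statements: how many women were told the same day, and how much sooner the typical woman was told. In addition, an outcome with an assigned analysis but no entry in the outcome list has no stated population or unit.

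**Working it through.** **Inputs.** The documents give about 1 hour for pathway 1, laboratory transport for pathway 2, and 40 hrHPV-positive women per arm (sample-size text in Outcomes). They give no same-day share, no laboratory turnaround and no figure for any time outcome, so there is no plan figure to reproduce. It is also not stated whether notification time is for all women tested or only those who are positive. The calculations below assume 40 per arm.

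**Step 1: proportionality.** Let s be the share of pathway 1 told on the day of the test, and assume that no laboratory result is given that day. The day-0 hazard is s in pathway 1 and 0 in pathway 2, so their ratio is unbounded for any s above 0. From day 1 the ratio is finite. With s = 90%, 0.90 × 40 = 36 women are told on day 0. Only 4 pathway 1 women then remain to be compared with 40 in pathway 2.

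**Step 2: estimability.** Suppose that all 40 pathway 1 women are told before any pathway 2 woman. With hazard ratio θ, and j pathway 1 women still waiting, each pathway 1 event contributes θ / (jθ + 40) to the partial likelihood, for j = 40 down to 1. Each pathway 2 event contributes a constant. Every factor rises with θ towards 1/j, so there is no maximum and no finite estimate. If all 40 are tied on day 0, the Breslow form (θ / (40θ + 40)) to the power 40 also rises without a maximum.

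**Step 3: size short of full separation.** These are simulations with 40 per arm, untied times, an assumed lognormal pathway 2 time with median 6 days, and an assumed median of 3 days for pathway 1 women not told the same day.

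| Same-day share, pathway 1 | Runs with complete separation | Median HR in the other runs |
|---|---|---|
| 50% | 0% | 4.9 |
| 80% | 0% | 8.7 |
| 90% | 4% | 14 |
| 95% | 23% | 21 |
| 100% | 100% | none |

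The laboratory assumption is the same in every row. Only the same-day share changes, and the HR moves with it.

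**Step 4: ties and the period after day 0.** With times recorded in days:
- 90% same-day, assumed pathway 2 median 3 days: HR 3.9 (Breslow) or 5.5 (Efron), and about 1 after day 0.
- 70% same-day, assumed pathway 2 median 4 days: HR 3.0 to 3.7 according to the tie method, and about 1.6 after day 0.

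**Step 5: the other two methods.** Kaplan-Meier needs no proportionality. The log-rank statistic stays finite under the full separation of step 2:
- observed pathway 1 events = 40
- expected = Σ j/(j + 40), j = 1 to 40, = 12.5
- variance = Σ 40j/(j + 40)² = 7.85
- z = (40 − 12.5)/√7.85 = 9.8

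**Step 6: colposcopy times.** The sentence that names the survival methods names time to colposcopy. Those methods keep a woman who never attends as a censored observation. The linear-regression rule names no outcome, yet the two colposcopy times are the only continuous quantitative outcomes listed, so the wording overlaps. The two routes can differ sharply. The next simulations use 40 per arm, 84% versus 56.4% seen by 20 working days, and assumed censoring at 120 working days. With assumed non-attendance of 5% (pathway 1) and 30% (pathway 2), power is 14% for a t test in attenders and 92% for the log-rank test. With 10% in both arms the order reverses, 98% against 63%. The two analyses answer different questions, so it should be plain which one applies.

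**The case against.** The strongest reply is that the Cox model will probably run. Same-visit notification is stated as an intention, women who cannot stay are contacted later, and some samples are taken at home. At 90% same-day or below, complete separation was rare or absent under the assumptions of step 3, and if the outcome covers all women tested, the larger numbers make it rarer still. This stands, and it limits the claim: a reader might infer that the Cox analysis is bound to fail, and the documents do not support that. It does not restore proportionality, because the exceptions leave the day-0 block in one arm only.

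Tie handling and checks of proportional hazards are ordinary content for an analysis plan that is not shown. Their absence is not the point. The point is the choice of summary, which the article does state.

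A reader might also infer from the general rules on continuous outcomes that women who never attend would be dropped from the time-to-colposcopy analysis. The documents do not support this. The specific sentence assigns survival methods to time to colposcopy and governs over a general rule that names no outcome. The t and Mann-Whitney sentence can apply to baseline variables such as age. The 20- and 40-working-day proportions are taken among all hrHPV-positive women, so non-attendance is visible there too. Only the overlap in wording remains.

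**Conclusion.** The point holds for one of the three methods named and one of the two time variables: the Cox hazard ratio for time to notification. That proportional hazards is not to be expected follows from the design, given only that laboratory results are seldom or never given on the day of the test. That the hazard ratio has no finite estimate holds only if every pathway 1 woman is told before the first pathway 2 woman. The range of about 4.9 to 21, and the gap between tie methods, rest on assumed turnaround times and same-day shares and on 40 per arm. The direction is secure, the numbers are not.

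The absence of time to notification from the Outcomes section can be read directly from the text and needs no assumption. For the colposcopy times only a clarification is needed. Severity is low: the primary outcome and its analysis are unaffected.

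**What to change.** 1. For time to notification, drop the Cox hazard ratio. Report the proportion told on the day of the test and the difference in median time, each with a 95% CI, beside the Kaplan-Meier curves and log-rank test already planned. Give the same-day comparison as a difference in proportions: if no pathway 2 woman is told the same day, an odds ratio or relative risk has no finite estimate either. Take the medians from the Kaplan-Meier curves so that women not yet told are kept. Both measures are needed, because once more than half of pathway 1 is told the same day its median in days is 0 and the difference is simply the pathway 2 median.
2. Add time to notification to the secondary outcomes, stating its population (all tested or hrHPV-positive) and unit (hours or days).
3. Add one sentence: the survival methods, with all hrHPV-positive women included and non-attenders censored, govern both test-to-colposcopy and referral-to-colposcopy times, and the general linear-regression and t/Mann-Whitney rules do not apply to them. Restricted mean time is an optional extra.

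The cost is a few sentences and standard procedures in SAS or R, with no new data. The downside is that notification time will have no single hazard ratio.
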